## Methods and analysis

### Design

This study is a two-arm parallel randomised controlled trial with a 1:1 allocation. The study will divide the patients into two groups: the intervention group, in which the patients will receive S-VR therapy through a VR device (head-mounted display) mounted on the patients’ heads during chemotherapy plus standard care (daily routine care in administration of chemotherapy drugs), and the control group, in which the patients will receive standard care and guided imagery therapy with leaflets containing instructions for techniques for relaxing through image visualisation. The group allocation will be implemented using the envelope concealment method, and the outcome assessor will be blinded to the group allocation during data collection. The protocol has been designed in accordance with the Standard Protocol Items: Recommendations for Interventional Trials and its checklist.^30 31^
Figure 1 presents the modified Consolidated Standards of Reporting Trials^32^ flow diagram.^32^

**Figure 1 F1:**
[figure not shown]
Modified Consolidated Standards of Reporting Trials flow diagram.

### Setting

The DIY Province will be the study location because it has the highest prevalence of cancer in Indonesia. The national prevalence of cancer is 1.79/1000 population, whereas the prevalence in the DIY Province is 4.86/1000 population, with 23% of these patients undergoing chemotherapy treatment.^2^ This study will be conducted at the One Day Chemotherapy Polyclinic ‘Tulip’ Integrated Cancer Unit of [name] Hospital, Yogyakarta, Indonesia. According to the annual report of the service performance of the Integrated Cancer Unit of [name] Hospital, the number of visits by patients with cancer was 100 614 people in 2019, an increase of 19.8% from the previous year.

### Patient and public involvement

The protocol has been designed in close collaboration between the School of Nursing, Taipei Medical University, and the Master of Nursing Programme, Universitas Gadjah Mada, with strong support from [name] Hospital, Yogyakarta, Indonesia. We work with patients with cancer undergoing chemotherapy under the Integrated Cancer Unit at [name] Hospital, Yogyakarta, Indonesia. A patient with cancer undergoing chemotherapy was enrolled in this intervention programme and completed the study evaluation. Valuable input, preference and evaluation on the part of both patients and hospital institutions have been invaluable in the development of this intervention; thus, we hope that the findings from this randomized controlled trial will be disseminated to local, regional and national policymakers as well as an international scientific audience.

### Population and sample

The target population is patients with cancer who will undergo chemotherapy at the ‘Tulip’ Integrated Cancer Unit of [name] Hospital. The inclusion criteria for this study are as follows:

Being a patient with cancer receiving chemotherapy in all cycles.Being aged ≥18 years.Having a performance status (Eastern Cooperative Oncology Group, ECOG Score) of 0–2.Being able to understand and sign the informed consent form.

Respondents who meet the following exclusion criteria will be excluded from the study:

Being a patient with cancer with a history of skull structure or cervical spine abnormalities that may complicate the use of VR devices.Being a patient with cancer with cognitive, visual and hearing impairment; or having a chemo port.Being a patient with a history of epilepsy, seizures, vertigo or visually induced motion sickness.

### Sample size calculation

The sample size was calculated using free-to use software, namely G*Power for Windows V.3.1.9.6.^33^ The effect size is 0.81, type 1 error (α)=5% (two-tailed), power (1−β) 90% and the allocation ratio between the groups is 1:1. The effect size was set with reference to previous studies with similar outcomes.^9^ According to the G*Power calculation, the study sample size should be 34 per group. With consideration of an expected dropout rate of 15%, the sample size was increased to 40 per group.

The participant dropout criteria are as follows:

The patient being unwilling to continue the sequence of the study process (lost to follow-up).The patients experiencing drug extravasation incidents or severe side effects during chemotherapy.

The consecutive sampling technique will be applied. This non-probability sampling method involves recruiting all individuals from the accessible population during a given time interval or for a specific sample size. Patients with cancer who have scheduled chemotherapy and meet the requirements of the data collection time will be asked to participate in the study.

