### Safety and side effect management

The intervention of this study is not associated with any significant side effects because it does not involve invasive procedures and is administered for a short period (one chemotherapy cycle). However, we predict that the participants will feel discomfort both while using the VR and during chemotherapy and will record their levels of discomfort on a monitoring sheet. The Virtual Reality Symptom Questionnaire, which was developed by Ames *et al*,^44^ will be administered to patients after the VR intervention in order to assess the possibility of cybersickness, a form of motion sickness caused by exposure to VR. The questionnaire evaluates eight general physical side effects (general discomfort, fatigue, boredom, drowsiness, headache, dizziness, concentration difficulties and nausea) and five visual effects (tired eyes, aching eyes, eyestrain, blurred vision and difficulties focusing). The scoring was modified to a 4-point scale (the original score consisted of a 6-point scale), from 0 to 4 (represented of none, mild, moderate, severe) with 0 indicating the absence of the symptom and 4 indicating its severity. During the study, the researchers will clearly indicate that they can be contacted should the participants have any VR-related problems or complaints or if something unexpected occurs.

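### Extravasation and severe side effects count as dropout after randomisation, which appears to take patients with discomfort-related events out of the comfort comparison

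*Protocol article*

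**What the plan says.** The Sample size calculation section gives two criteria for participant dropout. One is withdrawal: "The patient being unwilling to continue the sequence of the study process (lost to follow-up"). The other is event-based and separate: "The patients experiencing drug extravasation incidents or severe side effects during chemotherapy". The same section plans 34 evaluable patients per group and raises this to 40 for an expected 15% dropout.

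Other sections fix the timing:

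- **Allocation.** Under Patient recruitment, the envelope is opened after the pretest, and the patient is then sent to the room for the allocated arm.
- **Outcome.** Under Outcomes and in Table 2, the comfort questionnaire (SGCQ) is completed only at T0 and T4. T4 follows the end of the chemotherapy session.
- **Exposure.** Under Intervention, the headset is worn during chemotherapy. The Safety section expects some discomfort while using VR and plans a symptom questionnaire "to assess the possibility of cybersickness, a form of motion sickness caused by exposure to VR".
- **Analysis.** Data analysis specifies t-tests, or rank tests, on comfort before and after treatment. It does not say how patients who meet a dropout criterion are treated.

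**The concern.** The event criterion acts after randomisation and selects on something close to the primary outcome. The Introduction defines comfort as the absence of pain, distress, worry and unease, and extravasation or a severe reaction is a direct cause of the opposite. A patient dropped between T0 and T4 has no post-test comfort score, even if willing and able to give one.

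Two things are at stake. First, the wording does not restrict the cause of the side effects. Severe nausea or dizziness from the headset would meet it, and only one arm is exposed to that. If removals differ by arm, the groups compared are no longer the groups randomised. Second, even with equal removal, the comfort result would apply only to patients whose session passed without such an event.

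**Working it through.** **1. The plan's own figures.** Inputs from Sample size calculation: "The effect size is 0.81, type 1 error (α)=5% (two-tailed), power (1−β) 90"%, and "the allocation ratio between the groups is 1:1". For a two-sided t-test the noncentrality is d × √(n/2). At n = 34 this is 0.81 × √17 = 3.34 on 66 degrees of freedom. Exact power is 0.8998 at 33 per group and 0.9084 at 34, so 34 reproduces. Inflation: 34 / (1 − 0.15) = 40, which also reproduces. The arithmetic is sound. It also shows how dropouts are viewed: 40 × 0.15 = 6 patients per arm are expected to add nothing to the comparison.

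**2. Order of events.** Consent and T0 comfort → envelope opened → chemotherapy room → IV access and premedication → VR or imagery → rest of session → T4 comfort. An event during chemotherapy therefore falls after allocation and before the only post-test score.

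**3. Size of the shift.** Let p be the proportion removed in an arm and δ how much lower removed patients score than retained patients in that arm. The mean of all patients is the retained mean minus p × δ, so the between-arm contrast among completers shifts by (p_VR − p_control) × δ. The article gives no event rates by arm, so p and δ are assumptions.

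| Removed, VR / control | δ | Shift towards VR |
|---|---|---|
| 15% / 5% | 1 SD | 0.10 SD (0.10 / 0.81 = 12%) |
| 15% / 5% | 1.5 SD | 0.15 SD |
| 15% / 10% | 1 SD | 0.05 SD |
| equal | any | 0 |

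**4. A wider range.** Suppose that in each arm exactly the lowest scorers are removed. The retained mean then rises by φ(z_p) / (1 − p), which is 0.109 SD at 5% and 0.274 SD at 15%. If removal correlates only 0.5 with comfort, these values halve. False-positive rates come from 40,000 simulated trials of 40 per arm with no true effect and a nominal two-sided 5% test.

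| Removed, VR / control | Link to comfort | Shift | False-positive rate |
|---|---|---|---|
| 6 / 2 (15% / 5%) | lowest scorers | 0.17 SD | 0.15 |
| 6 / 0 (15% / 0%) | lowest scorers | 0.27 SD | 0.24 |
| 6 / 2 | correlation 0.5 | 0.08 SD | 0.07 |
| 6 / 0 | correlation 0.5 | 0.14 SD | 0.09 |

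**5. Keeping everyone.** With all 40 per group analysed and an effect of 0.81, power is 0.947. Retaining these patients needs no larger sample, provided the effect stays near 0.81.

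**The case against.** The case on the other side is that the article lists dropout criteria under a sample-size inflation and never defines a completers-only analysis set. Analysis sets and missing-data rules may stand in a document not shown. Extravasation and drug toxicity should also balance across arms on average. Much of this stands, and it limits the point in five ways.

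- **Exclusion is inferred.** It follows from the word dropout, the inflation from 34 to 40 and the single post-test. A reader might take it as stated, but it is not.
- **Not every patient made ill by VR is affected.** Only severe events qualify. The Safety section predicts discomfort and expects no significant side effects from the intervention. The eligibility criteria exclude patients with vertigo or visually induced motion sickness, and the video length was chosen partly to prevent motion sickness.
- **VR harm is not shown to be hidden.** The symptom questionnaire is given after VR, and nothing says its results are discarded for dropouts.
- **The withdrawal criterion does not show that patients who merely decline VR are lost.** It concerns unwillingness to continue with the study process. No sentence describes a patient who refuses the headset but remains available for T4.
- **Bias towards VR is conditional.** It needs more removals in the VR arm. The 15% against 5% split is illustrative. It averages 10%, below the budgeted 15%, which also covers withdrawals. The resulting 0.10 SD is less than half the standard error of the contrast (√(2/40) = 0.22 SD to √(2/34) = 0.24 SD).

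What the objection does not remove is the rule itself. The article names an event-based dropout criterion separate from withdrawal, so a later analysis plan would have to overrule that text rather than fill a gap.

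**Conclusion.** The point holds in a limited form. As written, the plan counts as dropout a group defined by post-randomisation events closely tied to the primary outcome, and its sample-size reasoning implies that these patients are not analysed. Whether this biases the comparison depends on whether removal differs by arm, which the article leaves open and does not quantify.

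Under the stated assumptions (15% against 5% removed, 1 SD lower comfort) the shift is 0.10 SD, about 12% of the planned effect. The other unequal-removal cases worked above run from 0.05 to 0.27 SD, and the top value needs six removals against none, all of them the lowest scorers. With equal removal the expected bias is about zero, but the estimate then describes only patients free of such events. The documents do not support a firmer claim that the trial will favour VR or conceal its harms.

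**What to change.** For study follow-up and analysis only, with clinical care unchanged:

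1. Stop counting extravasation and severe side effects as dropout.
2. Keep these patients in follow-up, together with any who stop VR or imagery early but agree to further data collection. Collect the T4 SGCQ where the patient is able and willing, and say when it is taken if the session is cut short.
3. Analyse them in the allocated arm.
4. Count as lost only those who withdraw from data collection or have no T4 score. Report numbers and reasons by arm.
5. Add a sensitivity analysis in which missing comfort scores may be worse than observed ones, for example delta-adjusted imputation. Standard multiple imputation alone assumes data missing at random. With no comfort score between T0 and T4, it would not reliably repair loss that depends on comfort.

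The cost is a change of wording and one more analysis, with no increase in sample size. T4 will not be obtainable from every patient with a severe reaction, which is why item 5 is needed. The estimate may be slightly smaller or more variable than a completers-only result.

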### Participant characteristics and study outcomes

#### Participant characteristics

A questionnaire will be used to collect patient demographic data, including age, sex, education level, marital status, occupation, income and assistance during chemotherapy, and clinical characteristics, including the type of cancer, body surface area (height and weight), cancer stage, duration of diagnosis, chemotherapy cycle and ECOG Score.

#### Outcomes

The primary and secondary outcomes are summarised in table 1.

**Table 1 T1:** Study outcomes

Outcome	Measurement tool	Score	Interpretation
Primary			
Comfort	The Shortened General Comfort Questionnaire, Indonesian version^41^	Likert Scale—1 (strongly disagree) to 6 (strongly agree)	Higher scores indicate higher levels of comfort.
Secondary			
Symptom management self-efficacy	The Self-Efficacy of Cancer Symptom Self-Management Scale^42^	Likert Scale—1 (not at all sure) to 10 (very sure)	Higher scores indicate higher levels of self-efficacy.
Anxiety	The Visual Analogue Scale for Anxiety^43 44^	A horizontal line with a scale of 100 mm	Higher scores indicate greater anxiety.
Pain	The Numerical Pain Rating Scale^45^	Numerical scale—0 to 10 (11-point scale)	Higher scores indicate greater pain.
Pulse rate	Digital sphygmomanometer	Beats per minute (bpm)	An adult’s regular resting heart rate ranges from 60 bpm to 100 bpm.
Blood pressure	Digital sphygmomanometer	Millimetre of mercury (mm Hg)	Systolic pressure above 90 mm Hg and lower than 120 mm Hg and diastolic pressure between 60 mm Hg and 80 mm Hg

Comfort of patients with cancer is measured using the Shortened General Comfort Questionnaire (SGCQ) instrument by Katharine Kolcaba in 2006 which has been tested for validity and reliability in Indonesian version by Artanti *et al*.^34^ The validity test reported that Content Validity Index (CVI) of Item (I-CVI) and Scale (S-CVI) Score were both 1 (valid). Cronbach’s α score showed 0.769, meaning that the SGCQ Indonesian version is reliable. The SGCQ instrument describes individual comfort by assigning a Likert Score to 28 items. Likert Scores range from 1 (strongly disagree) to 6 (strongly agree). The highest total score is 168, and the lowest is 28.

Self-efficacy is measured by using the Self-Efficacy of Cancer Symptom Self-Management Scale (SE-CSSMS),^35^ which consists of six question items with a value range of 1 (not at all sure) to 10 (very sure). SE-CSSMS has been tested for validity and reliability on patients with cancer in Indonesia.^35^ The CVI is 0.94. The r value is 0.467, which is greater than the r-table value of 0.12, so these results state that the six items in the symptom management self-efficacy instrument are valid. The reliability test results showed that the Cronbach α value is 0.90 (>0.70), so the measuring instrument is reliable.

Anxiety is measured using the Visual Analogue Scale for Anxiety (VAS-A) in the form of a horizontal line with a scale of 100 mm or 10 cm, with the left by the words ‘not at all anxious’ and on the right by ‘extremely anxious’.^36 37^ VAS-A has a sensitivity of 76.8%, specifications of 64.9% and internal reliability consistency (Cronbach’s α ≥0.7).^36 37^

Pain is measured using the Numerical Rating Scale (NRS). The NRS consists of numerical scale; from 0 to 100 (101-point scale), 0 to 10 (11-point scale) or 1 to 10 (10-point scale). This study will use a 0–10 NRS due to it provides more sufficient sensitivity to measure pain in most patients with cancer.^38^ The NRS has been declared valid and reliable for subjective measurement of cancer pain, both due to adverse effects of cytotoxic agents, cancer treatment procedures (surgery, radiotherapy and chemotherapy) and the malignancy of the cancer itself.^39^

Pulse rate and blood pressure (systolic and diastolic pressure) are measured using an automatic digital sphygmomanometer. According to American Heart Association, the regular resting heart rate for adults is 60–100 beats per minute, and systolic blood pressure is above 90 mm Hg and less than 120 mm Hg, with a diastolic pressure between 60 mm Hg and less than 80 mm Hg.^40^

Comfort and self-efficacy for symptom management will be measured at two time points: at baseline (before chemotherapy premedication) and post-test (after the chemotherapy session is completed). Anxiety, pain and vital signs (pulse rate and blood pressure) will be measured at five time points: thrice at pretest (baseline data collection, before the installation of intravenous access and before administration of VR intervention) and twice at post-test (immediately after intervention and after the chemotherapy session is completed). The timeline of the data collection and measurement is presented in table 2.

**Table 2 T2:** Timeline of data collection and measurements

Assessment/measurement instrument	Study period				
	T0	T1	T2	T3	T4
Demographic variables	**X**				
Clinical characteristics	**X**				
SGCQ	**X**				**X**
SE-CSSMS	**X**				**X**
VAS-A	**X**	**X**	**X**	**X**	**X**
NPRS	**X**	**X**	**X**	**X**	**X**
Blood pressure	**X**	**X**	**X**	**X**	**X**
Pulse rate	**X**	**X**	**X**	**X**	**X**

T0: baseline data collection (after prechemotherapy assessment and obtaining signed informed consent); T1: before intravenous installation/premedication; T2: before the start of the intervention; T3: immediately after the intervention; T4: after completion of one chemotherapy cycle.

NPRS, Numerical Pain Rating Scale; SE-CSSMS, Self-Efficacy of Cancer Symptom Self-Management Scale; SGCQ, Shortened General Comfort Questionnaire; VAS-A, Visual Analogue Scale for Anxiety.

### Randomisation and concealment

The researchers will screen to identify patients who are eligible to participate in the study. The patients’ medical records will be evaluated to verify their baseline information (eg, anthropometric data, laboratory data, patient identification data and laboratory results). An allocation sequence will be generated through simple randomisation of the study participants by using a formula on the Microsoft Excel program (the RANDBETWEEN function), and the allocation sequence will be concealed in sealed envelopes. Thereafter, the participants in the intervention and control groups will receive envelopes containing random numbers generated using the randomisation procedure. The outcome assessor (the nurse appointed by the researcher to be responsible for outcome data collection) and data analysts will be blinded to the participant allocation. Due to the technical nature of the VR interventions, it was difficult to blind the study participants. Thus, to minimise potential methodological bias, the outcome assessor and data analysts will be blinded.^41^

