**Methods and analysis:**

We will recruit 80 patients from the One Day Chemotherapy ‘Tulip’ Center of [name] Hospital, Yogyakarta, Indonesia. This will be a two-arm parallel randomised controlled trial, with a 1:1 allocation and the primary outcome assessor blinded. This study will be divided into two groups: (1) an intervention group, with participants receiving 360° panoramic video content and music relaxation intervention through a VR device (head-mounted display) placed on their head during chemotherapy for ±10 min plus standard care and (2) a control group, with participants receiving guided imagery relaxation therapy in the form of a leaflet plus standard care. We will measure the outcomes after one chemotherapy cycle for each participant. The primary outcome is the effectiveness of the S-VR in improving the comfort of patients. The secondary outcome is the effect of the S-VR on the patients’ symptom management self-efficacy, pain, anxiety, blood pressure (systolic blood pressure and diastolic blood pressure) and pulse rate.

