### Patient recruitment

Recruitment will be conducted from April to July 2023. Patients who are scheduled for chemotherapy will be assessed by the nurse on duty, who will review their latest laboratory results, medical records, vital signs and ECG results, to determine whether they are eligible to undergo chemotherapy. The patients who pass the screening process will be asked whether they are willing to be involved in the study and will be asked to sign the informed consent form. Patients who are willing and who sign the informed consent form will be given a sealed envelope containing a random number indicating their group allocation. The participants will be evaluated (pretest) by the outcome assessor (research nurse) before they enter the chemotherapy room. After the evaluation, the researcher will open each participant’s envelope and see the random number that they have been assigned (without the knowledge of the participants or the outcome assessor). If the number assigned is between 1 and 40, the participant will be directed to the chemotherapy room on the east side of the hospital (intervention group); if the number is between 41 and 80, the participant will be directed to the chemotherapy room on the west side of the hospital (control group). We will for the participants in the intervention and control groups to be directed to different chemotherapy rooms, and a research assistant (RA) will accompany the participants to the rooms to minimise contamination of information between participants, between participants and intervention providers and between the nurses or doctors on duty.^42^

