### Data analysis

The collected data will be processed using IBM SPSS statistical software V.23 for Windows through editing, coding and data entry processes. The statistician will be blinded to the study outcomes and will conduct analyses on the basis of the labelling of the groups. For the treatment group, the demographic and clinical variables recorded at enrolment will be tabulated. The descriptive statistics will be presented as numbers, means, SDs, medians, minimums and maximums. Homogeneity and normality tests will be conducted before the bivariate analysis test. A homogeneity test for categorical data (age, sex, education level, marital status, occupation, income, the presence of a family member or caregiver during chemotherapy, type of cancer, stage of cancer, duration of cancer diagnosis, chemotherapy cycle and ECOG Scores) will be performed using the χ^2^ test or Fisher’s test, whereas a homogeneity test for numerical data (height and weight) will be performed using Levene’s test if the data are normally distributed and using the Mann-Whitney U test if the data are not normally distributed. Both groups will be considered to be homogeneous if p>0.05. Bivariate analysis will be used to determine the differences in the mean scores for comfort level and symptom management self-efficacy before and after treatment in the intervention and control groups. If the data distribution is normal, we will use a paired t-test and independent t-test. However, if the data distribution is not normal, the non-parametric Wilcoxon and Mann-Whitney U tests will be used if significant differences are identified (p<0.05). For anxiety, pain and vital-sign (blood pressure and pulse rate) outcome measurement analysis, General Linear Model-Repeated Measure (GLM-RM) statistics will be used. The GLM-RM is a statistical test used for the comparative analysis of two unpaired numerical data groups with more than two measurements and is applied when the effect of a treatment or intervention is measured at different time points. If the data are not normally distributed, the repeated Mann-Whitney alternative test with Bonferroni correction will be used. The present study will use statistical method to adjust for potentially confounding effects of the S-VR intervention on the patient’s outcomes. These confounders include age, gender, education, cancer stage, chemotherapy cycle, assistance during chemotherapy and comorbidities. Multivariate model can handle identified confounders and minimise the bias effect of the intervention.^45^ Linear regression analysis will be applied by using the enter method. Adjustment by using this analysis can clarify that how much the confounders in the model distort the intervention and outcome.^46^

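### The trial is labelled primary-outcome-assessor blinded, but comfort is self-rated by unblinded patients, and the nurse's own blinding is unlikely to survive arm-specific rooms

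*Protocol article*

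**What the plan says.** The Abstract describes the design as "with a 1:1 allocation and the primary outcome assessor blinded". Randomisation and concealment admits that "it was difficult to blind the study participants" and offers the blinding of others as the remedy: "Thus, to minimise potential methodological bias, the outcome assessor and data analysts will be blinded". The same section gives one person the task of gathering outcomes: "The outcome assessor (the nurse appointed by the researcher to be responsible for outcome data collection".

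Patient recruitment places the pretest before the patient enters the chemotherapy room. The researcher then opens the envelope, keeping the number from patient and assessor, and the arms are separated by place: "We will for the participants in the intervention and control groups to be directed to different chemotherapy rooms". For the lower numbers, "the participant will be directed to the chemotherapy room on the east side of the hospital (intervention group"; the higher numbers go to the west room, which is the control room.

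In Outcomes, the SGCQ and the self-efficacy scale are taken at T0 and T4. Anxiety, pain, blood pressure and pulse are taken at all five time points, including "T2: before the start of the intervention; T3: immediately after the intervention". The Intervention section says the headset is worn during chemotherapy.

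On the analyst, Data analysis states: "The statistician will be blinded to the study outcomes". Randomisation and concealment instead has the data analysts blinded to allocation.

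**The concern.** Blinding the outcome assessor protects a result when the assessor's judgement produces the value. Here the primary value is the patient's own agreement with 28 statements, and the patient knows which session took place. The inference from hard-to-blind participants to a blinded nurse as the safeguard therefore does not work for the primary outcome.

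The arrangements also make it doubtful that the nurse stays blinded. If the person responsible for outcomes takes readings around the session in a room that serves one arm only, the arm is apparent. The sentence on the statistician adds a third problem, because an analyst cannot be blinded to the data being analysed.

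At stake is how much weight a reader gives the comfort result, and after it anxiety and pain. The label promises a protection that the primary outcome does not have, and the article's listed limitations do not mention this.

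**Working it through.** No figure in the plan depends on this point. The sample size (34 per group, 34 / 0.85 = 40 after 15% dropout) is unaffected. The check sets the sections side by side.

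**1. Who produces each value (Table 1 and Outcomes).**
- Rated by the patient: comfort, self-efficacy, anxiety, pain = 4 rows.
- Read from an automatic sphygmomanometer: pulse rate, blood pressure = 2 rows.
- So 4 of 6 rows, including the primary, are the patient's own rating. For these, blinding the nurse can limit only the nurse's influence on how the form is completed, not the patient's knowledge of the session.

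**2. When the values are taken (Table 2).**

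| Time | Measures | Count | SGCQ included |
|---|---|---|---|
| T0 | all six | 6 | yes |
| T1 | anxiety, pain, blood pressure, pulse | 4 | no |
| T2 | same four | 4 | no |
| T3 | same four | 4 | no |
| T4 | all six | 6 | yes |

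The total is 6 + 4 + 4 + 4 + 6 = 24 outcome entries per patient. T0 is the reading whose blinding is best supported: the pretest by the assessor precedes room entry and the opening of the envelope. T2 and T3 hold 4 + 4 = 8 entries, all secondary. The post-treatment SGCQ is at T4 only.

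**3. Whether the nurse can stay blinded after T0.** Four links are needed.
- The nurse takes the readings. Randomisation and concealment makes the nurse responsible for outcome collection, and no other collector is named.
- Room identifies arm. Stated in Patient recruitment: east is intervention, west is control.
- The intervention is visible. Stated in Intervention: a head-mounted display worn during chemotherapy.
- The readings are taken in the room. **Not stated.** It is inferred because T3 comes immediately after a session given during chemotherapy, and no procedure for taking it elsewhere is described.

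Three links rest on the text and one is an inference, strongest for T3. To reach the primary outcome a fifth link is needed: that the same nurse administers the SGCQ at T4. The document gives neither the person nor the place for T4.

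**4. The analyst.** Randomisation and concealment says blinded to allocation; Data analysis says blinded to outcomes. Both cannot describe the same safeguard, and only the first is possible for someone analysing outcomes.

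**The case against.** The best defence is disclosure. The article never claims that participants are blinded, says openly that this was difficult, and calls its outcomes patient-reported. A headset cannot be disguised, so this limit comes with the intervention. The control arm also receives about 10 minutes of relaxation guided by a research assistant, which balances contact and may reduce differences in expectation. All of this stands. It does not rescue the Abstract's label, which attaches blinding to the primary outcome through a person who does not rate it.

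It is also fair that who stands where at T1–T4 is operational detail that a condensed article may leave out. That is why the point about the nurse is an inference. Likewise, the statistician sentence is probably loose wording, since it goes on to say that analysis is by group label; it needs a correction and does not show an unblinded analyst.

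A reader might infer more than the documents support:
- *That the 1–40 / 41–80 numbers reveal the arm to the assessor or analyst.* The number is withheld from the assessor, and nothing makes it the participant identifier or puts it in the analysis file. The same holds for the VR symptom questionnaire and the analyst.
- *That the nurse is certain to know the arm, or that expectation enters every reading after T0.* The first needs the nurse to be in the room. The second overlooks the automatic device, which leaves little room for observer judgement on blood pressure and pulse.
- *That a specific inflation of the false-positive rate follows.* Any such figure needs an assumed shift in patients' ratings, for which the documents give no basis. It would describe patient expectation, which neither a blinded nurse nor a relocated form removes.

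**Conclusion.** The point holds in two parts of different strength. First, from the text itself: the primary outcome is rated by patients who are not blinded, so the claim of a blinded primary outcome assessor gives the trial a property its primary outcome does not have. Second, as a strong inference: the nurse's blinding is unlikely to survive fixed arm-specific rooms and readings immediately around a visible session. This directly concerns secondary outcomes at T2 and T3, and extends to the SGCQ only if the same nurse also administers it at T4. Separately, the two statements on what the statistician is blinded to conflict.

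No numerical size can be given. The reach is four of six outcome rows self-rated, and eight T2/T3 entries per patient whose blinding is doubtful. This is a matter of correcting the claim and tightening one procedure; it does not invalidate the comparison or change the sample size.

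**What to change.** - In the Abstract, Design, and Randomisation and concealment, describe the trial as open-label to participants with a patient-reported primary outcome, and limit any assessor-blinding claim to readings where it can hold.
- Have the T4 SGCQ, self-efficacy, anxiety and pain forms completed by the patient alone in a common area outside both arm-specific rooms, and collected by a nurse not told the allocation.
- State who takes the T1–T3 readings and where, and report any taken in the room as not reliably blinded. Reassigning them to the research assistant is no improvement, because that person delivers the session.
- In Data analysis, change the statement to blinded to group allocation.
- As a precaution only, use a participant identifier unrelated to the 1–80 allocation number, and keep VR-only data out of the blinded analysis file.

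The separate rooms can stay, since they serve to limit contamination. The cost is a less favourable blinding claim, some rewording, and moving one assessment with existing staff; no extra patients are needed. Patient expectation remains and should be named as a limitation.
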